**Materials and Methods**

**Eligible participants**

Patients with symptomatic PAD will be recruited from Hospitals of São Paulo, Brazil. Patients will be included if they present a) Age > 40 years old; b) Ankle brachial index (ABI) < 0.90 in one or both limbs; c) if woman in post-menopausal period without hormone replacement therapy; and d) able to perform physical exercise in upper and lower limbs.

After agreeing to participate in the study, each patient will undergo a clinical evaluation. To confirm PAD diagnosis, ABI will be assessed in accordance with previous guidelines [1]. Briefly, ABI will be measured as the highest systolic blood pressure in the posterior tibial or dorsalispedis artery divided by the highest systolic blood pressure in the brachial artery. Blood pressure measurements will be recorded in both limbs using a doppler vascular monitor (DV160, Medmega, Brazil) and a sphygmomanometer.

To identify possible cardiovascular abnormalities during exercise, patients will be submitted to maximal treadmill test with a specific protocol for PAD population [2]. The test will start at a constant speed of 3.2 km/h, with 2% incline increments every two minutes until exhaustion. During the test, heart rate will be continuously monitored by an electrocardiogram. BP will be obtained at every two minutes using a mercury sphygmomanometer. It will be included only patients with no restrictions to perform physical exercise training.

**Study design**

This is randomized clinical trial with single-blind data collection. The protocol study will be conducted according to the principles of the Declaration of Helsinki and with the ethical principles governing research involving human subjects stipulated in Resolution 466/2012 of the Brazilian National Board of Health. The study protocol was approved by the Research Ethics Committee of Human Research of Hospital Israelita Albert Einstein, Brazil (February 2020 - CAAE: 81187317.6.0000.0071). All participants will read and sign an informed consent form before enrollment. Participation will be voluntary, and all ethical principles of confidentiality and data protection will be maintained.

Patients will perform two visits with an interval of at least 48 hours. In the first visit, patients will perform the functional tests (i.e. 6-min walk test, 2 minute step test [2 MST], handgrip test, walking impairment questionnaire [WIQ], walking estimated limitation calculated by history [WELCH], Baltimore activity scale for intermittent claudication, and short physical performance battery [SPPB]), cognitive assessment and answer the quality of life questionnaires (vascular quality of life questionnaire [VASCUQOL-6] and World Health Organization Quality of Life [WHOQOL brief]). On the second visit, patients will undergo cardiovascular assessments (i.e. office BP, ambulatory BP, central BP, heart rate variability, arterial stiffness and vascular function). After that, patients will be randomly placed in blocks to one of the three intervention groups (WT, ACT and control groups [CG]) and will be re-evaluated after 12 weeks. The random allocation sequence will be generated by Researcher Randomizer (https://www.randomizer.org). These data will be collected by a trained kinesiologist who will be blind to interventions.

During the study, patients will be excluded if they change their medication or present any health impairment that contraindicates the continuation of the practice of physical exercise during the study.

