| **Weeks** | **Bouts** | **Active exercise** | **Total active time** | **Interval** | **Total interval time** | **Total session time** |
| --- | --- | --- | --- | --- | --- | --- |
| 1-3 Week | 15 | 2’ | 30’ | 2’ | 30’ | 60’ |
| 4-6 Week | 14 | 3’ | 42’ | 1’30” | 19’30” | 62’ |
| 7-9 Week | 12 | 4’ | 48’ | 1’ | 11’ | 59’ |
| 10-12 Week | 10 | 5’ | 50’ | 1’ | 9’ | 59’ |

**Chart 1.** Periodization during the 12 weeks of training.

Patients randomized to CG will also attend to meetings with the researcher team twice week during the 12 weeks in order to minimize the effects of the patient's bi-weekly commitment and displacement to the training site, to minimize the influence of the patient-researcher contact and also minimize the convivial effect among the patients themselves, which will occur in the other two groups. During the meetings, patients will perform manual tasks with use of artistic materials, cultural programs, cooking classes and home care, without any exercise component.

All patients included in the study will also receive recommendations to increase levels of physical activity, which is the standard recommendation for clinical treatment for these patients [4].

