**Primary outcome**

**Ambulatory blood pressure**

Ambulatory BP will be assessed by an oscillometric device (Dyna-MAPA, Cardios, Brasil) programmed to take measurements every 15 min for 24 hours. The recordings will only be accepted if at least 80% of the readings were successfully performed. Patients will be instructed to complete a diary to record the time of sleep, waking and daytime activities. Ambulatory data will be analysed using the averages of 24 h, awake and asleep periods [5].

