**Intervening variables**

In order to minimize the possible influences of intervening variables, and to ensure that the changes generated on outcomes will be caused by ACT or WT interventions, medications, dietary pattern, and physical activity levels will be monitored.

To control of medication, each week the researcher will be responsible for filling a container with the medications prescribed for the patient, according to the frequency, time and recommended dosage. At the end of the week (in the second weekly session), the researcher will check if the patient correctly took the medications. Patients will be followed during the 12 weeks period of intervention.

For food monitoring, before and after the intervention period, patient will be asked to fill a food diary for four days of the week, including at least one day of the weekend. Based on this information, it will be possible to analyze changes in the dietary pattern of the patients, as well as to estimate the caloric intake ingested before and after the intervention period.

Finally, patients will use a smartwatch (A300, Polar, Finland) that will estimate their physical activity levels. The POLAR A300 is a monitor coupled with a 3D accelerometer that records patient’s movements. Through it, it is possible to analyze the frequency, intensity and regularity of the movements and, consequently, to determine the physical activity levels. Patients will use this monitor for one week before the first evaluation and after the last week of training, allowing to identify possible changes in physical activity level with ACT, WT and CG interventions.

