**Statistical analysis**

**Power and sample size**

The sample size was determined by the a priori specific sample calculation for clinical trials involving parallel groups, in this case two-way ANOVA with repeated measures. Using GPower 3.1.9.2 software it was considered an effect size of 0.25; α of 0.05; power (1 - β) of 0.80; correlation coefficient between repeated measures of 0.6; non-spherical correction (ɛ) of 1 and three groups two measures. Thus, the minimum total size reached 36 subjects (12 per group) with 83% power. Considering the possibility of sample loss, the sample was inflated by 20%, resulting in a sample of 45 patients (15 per group).

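### Randomised patients who change medication or can no longer exercise are excluded, with no provision to measure their ambulatory blood pressure at 12 weeks

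*Protocol*

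**What the plan says.** The protocol's Study design section has patients "randomly placed in blocks to one of the three intervention groups (WT, ACT and control groups [CG]) and will be re-evaluated after 12 weeks". The same section then adds the rule: "patients will be excluded if they change their medication or present any health impairment that contraindicates the continuation of the practice of physical exercise". Its opening words, "During the study, patients will be excluded", place it in the period that includes the 12 weeks after randomisation. It names no drug class, direction of change or arm.

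Four other places bear on it:

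- **Primary outcome, Ambulatory blood pressure:** "Ambulatory data will be analysed using the averages of 24 h, awake and asleep periods".
- **Interventions:** the control group attends meetings "without any exercise component".
- **Intervening variables:** medication is monitored so that changes in outcome can be credited to training. The researcher fills a weekly container, and at the second weekly session "the researcher will check if the patient correctly took the medications".
- **Power and sample size:** 36 patients with 83% power, then "Considering the possibility of sample loss, the sample was inflated by 20" per cent, giving 45.

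No section says that an excluded patient attends the 12-week assessment or is analysed in the allocated arm.

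**The concern.** Randomisation makes the three arms comparable at baseline. A rule that removes patients for events after baseline keeps them comparable only if those events are unrelated to outcome and arm. There are two reasons to doubt that here.

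First, a rule on any medication change includes antihypertensive changes. These respond to BP, which is the primary outcome. If training lowers BP, the reasons to raise or reduce treatment will differ between arms, and so may the patients who remain.

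Second, the health limb is about fitness to continue exercise. In the two training arms that question arises at every session. In the control arm there is no exercise to continue, so the same impairment may be noticed or acted on less often. Training patients who develop such an impairment would also leave the comparison.

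At stake is whether the 12-week BP comparison is still a comparison of randomised groups. With 15 patients per arm, one or two exclusions are 1/15 = 7% to 2/15 = 13% of an arm.

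**Working it through.** **1. The plan's own sample size.** Inputs from Power and sample size: f = 0.25, alpha = 0.05, correlation rho = 0.6, epsilon = 1, k = 3 groups, m = 2 measures. For the group-by-time interaction in repeated-measures ANOVA:

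- Noncentrality: lambda = f² × N × m / (1 − rho), with degrees of freedom 2 and N − 3.
- N = 36: lambda = 0.0625 × 36 × 2 / 0.4 = 11.25; df 2 and 33; power 0.826. The stated 83% reproduces.
- N = 34 gives 0.7998 and N = 35 gives 0.813, so 36 is the smallest total with equal groups that reaches 0.80.
- Allowance: 36 / (1 − 0.20) = 45. This reproduces.

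**2. Power with and without the excluded patients.**

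| Patients analysed | lambda | Power |
|---|---|---|
| 45 (all measured) | 14.06 | 0.910 |
| 36 (20% lost for any reason, exclusions included) | 11.25 | 0.826 |
| 32.4 (a further 10% of the 36 lost to exclusions) | 10.125 | 0.777 |

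The first row ignores any dilution from patients whose medication changed. The third row applies only if exclusions come on top of the 20%.

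**3. Illustration of the selection effect.** Only rho = 0.6 is the protocol's. The rest is assumed: 24-h systolic BP mean 132 and SD 13 mmHg, true effect -6 mmHg in one exercise arm against control, and medication changed in a given share of patients whose follow-up BP is above 145 or below 115. Patients with a change are excluded, and the difference in mean change is computed in those who remain.

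| Share of triggered patients who change | Estimate after exclusion (mmHg) |
|---|---|
| 30% | -5.6 |
| 60% | -5.2 |
| 90% | -4.7 |

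At 60%, about 15% of controls and 16% of the exercise arm are excluded, so this case is nearly balanced by arm. If only upward changes occur (60% of those above 145), 9.5% of controls and 4.3% of the exercise arm are excluded and the estimate is -5.6.

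**4. No true effect.** Using SD 12 mmHg and rho 0.6, with the highest 10% or 20% of control follow-up values setting the cut-off:

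- Same cut-off in both arms: bias 0.
- Exclusion in controls only: a spurious difference of +0.9 (10%) or +1.7 mmHg (20%), against the exercise arm.

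**5. The same model with everyone kept.** Return to the model of step 3 at 60% changing, retain all patients, and assume a medication change moves BP by 5, 8 or 10 mmHg in the intended direction. The as-randomised estimates are -5.4, -5.1 and -4.9 mmHg, against -5.2 with exclusion. At 90% they are -5.1, -4.6 and -4.3, against -4.7.

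**The case against.** The strongest reply is that the attenuation in step 3 is measured against -6 mmHg, the effect had nobody's medication changed. An as-randomised analysis does not estimate that quantity either. Step 5 shows that it lands about as far from -6 as exclusion does, sometimes further. This stands. The simulated shortfall cannot be offered as the gain from the fix. The case for the fix is that it keeps the randomised comparison and collects data that would otherwise be lost.

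It can also be said that no section describes BP-guided changes of medication during the 12 weeks, that one rule is written for all arms, and that the simulated distortion of a true effect is conservative. These points stand too. Dependence on BP and arm is an inference from the nature of the rule. A reader might infer that exclusions will be driven by BP and by arm, or that a bias of a known percentage follows. The documents support neither. Other patterns, such as exclusions for reduced medication or for events linked to training, could push the estimate the other way.

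A reader might also infer that the trial falls to about 78% power. That requires a 10% loss beyond the 20% allowance. The protocol ties the allowance to sample loss in general, which can include exclusions; 36 then remain and the stated power holds. Nor does the rule remove patients for any health problem, only for one that rules out continuing exercise.

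Finally, the rule has a purpose: Intervening variables treats medication as something to control so that training can be credited with the change. The analysis set may also be defined in a statistical analysis plan that is not shown, and exclusion might mean only that the sessions stop. But the plain reading is removal from the study, and no analysis plan can recover a 12-week ambulatory recording that was never made.

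**Conclusion.** The point holds as a defect in follow-up. As written, the plan removes randomised patients for events that can be linked to the primary outcome and, through the exercise limb, to the arm, and does not provide for measuring them. The analysed groups may therefore differ from the randomised ones.

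No bias figure follows from the documents. On assumed inputs a true -6 mmHg becomes -5.6 to -4.7; with no true effect and the rule acting alike in all arms there is no bias. The sample size calculation is correct and its 83% is not contradicted. Measuring all 45 would give about 91% at the protocol's inputs, less whatever dilution medication changes cause. This is a cheap improvement, best made before follow-up begins because missed recordings cannot be recovered.

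**What to change.** Reword the exclusion sentence in Study design along these lines: *Participants who change medication or stop the exercise sessions remain in the study, are invited to the 12-week assessment, and are analysed in the arm to which they were randomised.*

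Alongside it:

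- Record the date, type and reason of each medication change and health event, by arm. The weekly medication check already provides the occasion.
- Add a supplementary analysis that treats a change in BP medication as an intercurrent event. This serves the stated aim of isolating the effect of training.

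The clinical decision on when exercise must stop is not altered.

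Cost: one sentence, some extra 12-week visits and one extra analysis; no larger sample. The main estimate will include the effects of medication changes, which is why the supplementary analysis is needed.

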**Interventions – Arm Crank Exercise, Treadmill Exercise, and Control Group**

Before starting the program, patients randomized to the ACT group will perform an adaptation session to familiarize with the ergometer and also to identify the training load. For this, patients will perform 10 bouts of two minutes exercising with minimum load with two minutes of passive interval between them. Patient will be instructed to maintain 50 revolutions per minute (RPM) during exercise. After that, to determine the training load for each session, patient will perform a progressive test where the load will be increased in 10 watts every minute of the test, following the protocol of two minutes of exercise with two minutes of interval until the patient report 13 – 15 values on the subjective effort perception scale (Borg scale - 6 to 20) [3].

Similarly, patients randomized to the WT group will perform 10 bouts of two minutes at 3.2 km/h without grade in the treadmill. After that, the load will be progressively increased in 0.3 km/h every minute of the test until the patient report 13 – 15 values at Borg scale. In both adaptation (ACT and WT), heart rate will be continuously monitored via heart rate monitor (Polar A300, Polar, Finland) and the subjective effort perception scale (Borg scale - 6 to 20) will be obtained at the end of each minute during the exercise.

Thus, during the first training sessions (i.e. ACT and WT), the workload corresponding to 13-15 values at Borg scale obtained in the progressive test will be employed. Arm Crank exercise Training and WT training will be performed twice a week for 12 weeks. The periodization of the training is shown in Chart 1. In the first 3 weeks, each session will consist of 15 bouts of two minutes of exercise with two minutes of passive recovery. After that, the exercise time will progressively increase by one minute every 3 weeks and the recovery period will be decreased, completing, at the end, a maximum volume of 10 bouts of 5 minutes of exercise with 1 minute of passive recovery. The intensity of both exercise groups will be determined by the intensity equivalent to the range of 13 – 15 of Borg scale (Borg scale - 6 to 20) [3]. In addition, the intensity assessment will be done during (each exercise bout) and at the end of each training session. All sessions will be supervised by a qualified kinesiologist with experience in vascular disease rehabilitation.

| **Weeks** | **Bouts** | **Active exercise** | **Total active time** | **Interval** | **Total interval time** | **Total session time** |
| --- | --- | --- | --- | --- | --- | --- |
| 1-3 Week | 15 | 2’ | 30’ | 2’ | 30’ | 60’ |
| 4-6 Week | 14 | 3’ | 42’ | 1’30” | 19’30” | 62’ |
| 7-9 Week | 12 | 4’ | 48’ | 1’ | 11’ | 59’ |
| 10-12 Week | 10 | 5’ | 50’ | 1’ | 9’ | 59’ |

**Chart 1.** Periodization during the 12 weeks of training.

Patients randomized to CG will also attend to meetings with the researcher team twice week during the 12 weeks in order to minimize the effects of the patient's bi-weekly commitment and displacement to the training site, to minimize the influence of the patient-researcher contact and also minimize the convivial effect among the patients themselves, which will occur in the other two groups. During the meetings, patients will perform manual tasks with use of artistic materials, cultural programs, cooking classes and home care, without any exercise component.

All patients included in the study will also receive recommendations to increase levels of physical activity, which is the standard recommendation for clinical treatment for these patients [4].

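### The control meetings include cooking classes that neither exercise arm receives, while diet, a listed intervening variable, is only monitored

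*Protocol*

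**What the plan says.** The Protocol section on interventions and the control group sets up an attention control: "Patients randomized to CG will also attend to meetings with the researcher team twice week during the 12 weeks". The stated aims are to offset the burden of attending and travelling, and "to minimize the influence of the patient-researcher contact and also minimize the convivial effect among the patients themselves". In these meetings "patients will perform manual tasks with use of artistic materials, cultural programs, cooking classes and home care, without any exercise component". No food-related activity is described for the arm crank (ACT) or walking (WT) groups. The one item of advice common to all three arms concerns activity: "All patients included in the study will also receive recommendations to increase levels of physical activity".

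The section Intervening variables opens with the purpose, "In order to minimize the possible influences of intervening variables", so that changes in outcomes can be attributed to the two training programmes. The measure it names is that "medications, dietary pattern, and physical activity levels will be monitored". For diet this means that, before and after the intervention period, the "patient will be asked to fill a food diary for four days of the week, including at least one day of the weekend". The diaries are to be used to analyse changes in dietary pattern and to estimate caloric intake.

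The primary outcome is ambulatory blood pressure (24-hour, awake and asleep averages).

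**The concern.** An attention control should match the training arms on contact, travel and company, and add nothing that might itself move the outcome. The protocol applies that principle to exercise, which it excludes from the meetings, but not to food. It then names diet as a factor to be kept from influencing the results.

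Any diet change prompted by the classes would arise after randomisation and in one arm only, so randomisation would not balance it. What is at stake is how the two comparisons with control on the primary outcome are interpreted. A difference, or the lack of one, could partly reflect what happened to diet in the control arm.

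**Working it through.** **1. The plan's own figure, and whether it depends on this point.** Power and sample size gives f = 0.25, α = 0.05, correlation 0.6, three groups, two measures and ε = 1. For the group-by-time interaction, the noncentrality is

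λ = f² × N × m / (1 − ρ) = 0.0625 × 36 × 2 / 0.4 = 11.25, with 2 and 33 degrees of freedom.

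This gives power 0.826, in agreement with the stated 83%. At N = 33 power is 0.786, so 36 is the smallest total with equal groups that reaches 0.80. Allowing for loss, 36 / (1 − 0.20) = 45, as stated. None of these inputs concerns the control activities, so the sample size stands whatever the meetings contain.

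**2. What each arm receives.**

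| Element | ACT | WT | Control |
| --- | --- | --- | --- |
| Two attendances a week for 12 weeks | yes | yes | yes |
| Contact with the research team and other patients | yes | yes | yes |
| Advice to be more active | yes | yes | yes |
| Supervised training | yes | yes | excluded |
| Cooking classes | none described | none described | yes |

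The first three rows are common to all arms and the fourth is the intended contrast. The last row also differs between the training arms and control, and none of the stated aims of the meetings calls for it. The number of control meetings is at most 2 × 12 = 24. The share given to cooking is not stated.

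**3. Where a diet effect would go.** Let c be the mean change in ambulatory pressure common to all arms, a and w the effects of ACT and WT, and b any change in control caused by the classes. The expected changes are c + a, c + w and c + b. Then:

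- ACT − control = a − b
- WT − control = w − b
- ACT − WT = a − w

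Both comparisons with control carry the same −b; the comparison of the two training arms carries none. If training lowers pressure and b is negative, the training effect looks smaller than it is. If b is positive, it looks larger. If training does nothing (a = w = 0), any non-zero b still leaves a difference of −b in both control comparisons. More patients would not reduce b.

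**4. What the food diary can do.** It is completed before and after the intervention, so it can show that diet changed differently between arms. It does not stop that from happening. Adjusting for the change would condition on a variable measured after randomisation and possibly affected by arm, which does not simply restore the unconfounded comparison.

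**5. Size of b.** The documents give no standard deviation for ambulatory pressure, no diet effect and no description of the classes. No figure for b can be derived, and zero is among the possible values.

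**The case against.** The strongest reply is that the dietary content is inferred. Cooking is one of four pastimes in a social programme, and nothing says that the classes teach nutrition or give advice on salt, fat or calories. The protocol also has a safeguard, since the diary looks directly for diet changes. How the diary data enter the analysis may be set out in a statistical analysis plan that is not at hand, so the absence of such a rule is no finding.

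Much of this stands. A reader might infer that the protocol requires diet to be equal across arms and so contradicts itself. It does not: the text speaks of minimising influence and of monitoring. A reader might also infer that the control group receives a dietary intervention, or that the trial is biased toward no effect. The documents support neither, because the content, number and direction of effect of the classes are all unstated.

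What the reply does not remove is the asymmetry. A food-related activity sits in one randomised arm, the exclusion covers exercise only, and monitoring detects rather than prevents. An analysis plan could not undo that, because it is a feature of what the arms receive.

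**Conclusion.** The point holds as an avoidable weakness in the design of the control programme, not as a demonstrated bias. A diet change tied to the control arm could shift ACT versus control and WT versus control on ambulatory pressure by an equal amount, in either direction. ACT versus WT, the sample size and the stated power are untouched.

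The conclusion rests on two things the protocol states, that cooking is offered to controls alone and that diet is an intervening variable for its outcomes. It also rests on one assumption, that cooking classes may change what patients eat. No magnitude can be attached from the documents. The change is worth making because it costs so little, not because harm has been shown.

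**What to change.** In the description of the control meetings, replace the cooking classes with the non-food activities already listed: artistic tasks, cultural programmes and home care. Extend the present exclusion of exercise content so that it also rules out dietary content. Keep the food diary as it is; it then serves as a check on unplanned diet changes.

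The cost is an edit to one sentence and slightly less variety for control patients. Meeting frequency, staffing, the matching of contact and company, and the sample size all stay the same.
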